# **７．****Matters Concerning Treatment for Study Participants**

## **7.1　Protocol Treatment Implementation Procedure**

**7.1.1　Informed Consent Acquisition**

• The attending surgeons shall confirm the subject's diagnosis and other eligibility criteria, provide a written explanation of this study, obtain the subject's understanding of the study, and acquire written informed consent from the subject.

• For tests conducted to determine eligibility, data obtained within 360 days prior to registration may be used, even if collected before consent acquisition.

**7.1.2　Registration and Randomization**

- After obtaining written consent, the attending surgeon shall reconfirm the subject's eligibility and register the subject in the study EDC system. Registered subjects shall be randomly assigned by the EDC system to either the plate group or the suture anchor group.

※Registration and randomization must be completed by the day before surgery.

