## **5.2　Clinical Study Design and Outline**

**5.2.1　Clinical Study Design**

1) Nature of the Study: Verification research

2) Randomization: Randomized Controlled

3) Blinding: Non-blinded

4) Control: Treatment control

5) Allocation: Parallel group comparisons

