**5.3　 Case Registration and Allocation Method**

1) Case Registration Method

The principal (or co-principal) investigator confirms that patients who have provided written informed consent meet all inclusion criteria and do not meet any exclusion criteria. Subsequently, personnel involved in this clinical study enter patient information into the EDC system to register and allocate the study subjects.

The subject's registration number and the method of laminectomy stabilization (plate method or suture anchor method) will be displayed in the EDC system and also recorded in a printable/downloadable PDF file. Study personnel shall confirm the subject's registration number and the assigned laminectomy stabilization method (plate method or suture anchor method), and record this information in the subject roster or print and retain the PDF containing the assignment results.

2) Allocation Method

- Allocation Method: Minimization Method
- Allocation Adjustment Factors: ① Facility, ② Age, ③ Gender, ④ Preoperative Diagnosis

[Rationale]

① Facility (Institute of Science Tokyo Hospital / Saiseikai Kawaguchi General Hospital / Saku Medical Center)

To account for potential differences between facilities in patient background, short-term outcomes, etc.

② Age (64 years or younger / 65–74 years / 75 years or older)

③ Gender (Male / Female)

Age and gender are common prognostic factors in treatment outcomes for DCM patients.

④ Preoperative Diagnosis (Cervical Spondylotic Myelopathy (CSM) / Ossification of the Posterior Longitudinal Ligament (OPLL))

Treatment prognosis has been reported to differ depending on the pathology.

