**5.4　 Expected Participation Period for Study Subjects**

Expected participation period: Approximately 2 years

(Period from registration to surgery: Maximum 90 days; Follow-up period: 2 years post-surgery)

After the expected participation period ends, if any adverse events suspected to be related to the study are identified, follow-up will continue until the principal (or sub-principal) investigator determines the study subject's safety is assured. Note that this follow-up period shall not be included in the study period.

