**7.1.3　Protocol Treatment**

- Protocol treatment (cervical laminoplasty) must be performed within 90 days of registration.
- If protocol treatment cannot be performed within 90 days for any reason, enter the reason for discontinuation in the case report form as “Protocol Treatment Discontinued”.
- If eligibility criteria are no longer met due to worsening of the primary disease or comorbidities between registration and the protocol treatment date (surgery date), the decision to continue study participation and perform surgery as protocol treatment is left to the discretion of the attending surgeon. The case report form must document that eligibility criteria were no longer met during the period from registration to the treatment date, along with details.
- Laminoplasty for DCM is performed using either the mini-plate or the suture-anchor.
- Surgery is performed under general anesthesia.
- A midline longitudinal skin incision is made from C2 to C7 in the prone position. Dissection is performed up to the medial facet joints.
- Perform a double-opening laminoplasty, expanding 2-4 laminae on the C3-6 vertebrae.
- Resect the tips of the spinous processes to expand the laminae. Use a high-speed drill to make a median longitudinal split in the midline of the laminae. Use the high-speed drill to create a groove at the medial aspect of the intervertebral joints, achieving a suitable hardness for lamina expansion. After creating a median longitudinal split and groove on all planned laminar expansions, gradually expand the lamina using a mucosal elevator. Medially transect the elevated ligamentum flavum, dissect adhesions to the dura mater, and confirm decompression by observing dura mater bulging. Control bleeding from the epidural venous plexus as needed.
- The attending surgeon shall perform the enlarged lamina fixation using either the plate method or the suture anchor method, according to the assignment results at registration.
- Dome-shaped laminectomy may be added to the cephalad and caudal laminae during lamina enlargement.
- Place a drain on the posterior aspect of the lamina prior to closure. Specifications and duration of drain placement are not stipulated.
- Regardless of any concomitant procedures, operative time, blood loss, and intraoperative/postoperative complications shall be included in the surgery. Details shall be recorded in the medical record (or surgical report) and case report.

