**7.6　 Individual Research Discontinuation Criteria**

The study will be discontinued if any of the following criteria are met.

1) If the protocol treatment (laminoplasty) cannot be performed within 90 days of registration.

2) If the research subject voluntarily requests to withdraw consent.

3) If, after registration, imaging or clinical diagnosis determines that laminoplasty is not indicated.

4) If intraoperative findings indicate laminoplasty is impossible or if cervical fusion is performed instead of laminoplasty.

5) If intraoperative complications (lamina fracture, vertebral body fracture) necessitate fixation during or after surgery

6) If a major deviation from the protocol is identified, such as violation of the Clinical Research Act and its enforcement regulations, selection criteria, or exclusion criteria

7) If compliance with the protocol becomes impossible

8) If the subject becomes pregnant

9) If the entire study is discontinued

10) If the research subject dies

11) Other cases where the principal investigator or attending surgeon determines continuation of the study is difficult

*The protocol treatment discontinuation date is defined as: the date of determination for cases 1-3), 5)-9), and 11); the surgery date for case 4); and the date of death for case 10).

[Rationale]

These criteria were established to ensure ethical research conduct and to safeguard the safety of research subjects.

[Procedure upon Discontinuation]

When discontinuing the study due to meeting discontinuation criteria, the principal investigator and co-investigators shall take appropriate measures for the subject and clearly document the date/timing of discontinuation, reason, and course of events in the medical records.

Furthermore, if consent is withdrawn after the start of the study treatment, efforts shall be made to clarify whether the cause is due to lack of efficacy of the drug, adverse events (or disease, etc.), or incidental events

(such as relocation). If clinically significant abnormalities (including laboratory values) are identified, appropriate tests shall be performed, and follow-up shall continue until values return to medically acceptable ranges or until the attending surgeon determines follow-up is unnecessary. For adverse events (or diseases, etc.) persisting after study discontinuation, follow-up shall continue until the event resolves or the attending surgeon determines follow-up is unnecessary.

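### The arm is displayed at registration, up to 90 days before surgery, so pre-operative exits can be decided with the arm known, and patients not operated on then leave the only efficacy set

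*Protocol*

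**What the plan says.** **Timing.** Section 7.1.2 has the attending surgeon reconfirm eligibility and register the patient, whereupon the EDC assigns the arm. The only limit stated there is "Registration and randomization must be completed by the day before surgery". Section 7.1.3 adds "Protocol treatment (cervical laminoplasty) must be performed within 90 days of registration", and section 5.4 gives the same interval: "Period from registration to surgery: Maximum 90 days; Follow-up period: 2 years post-surgery".

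**Who knows the arm.** Section 5.3 says that "the method of laminectomy stabilization (plate method or suture anchor method) will be displayed in the EDC system", together with the registration number, and that staff record it or keep the printout. Section 5.2.1 reads "Blinding: Non-blinded".

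**Exits before surgery.** Section 7.6 discontinues a subject under item 1 ("If the protocol treatment (laminoplasty) cannot be performed within 90 days of registration"), under item 2 for withdrawal of consent, and under item 3 when imaging or clinical diagnosis after registration shows that laminoplasty is not indicated. Section 7.1.3 separately lets the attending surgeon decide whether a patient whose eligibility has lapsed through worsening stays in the study.

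**Analysis.** Section 10.1.1 limits the FAS to randomised patients who received the protocol laminoplasty. Section 10.5 uses the FAS for every efficacy evaluation, and section 10.4 rules out imputation.

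**The concern.** The arm determines only how the opened laminae are held; the rest of the operation is common to both arms (section 7.1.3). Nothing in the design therefore needs the arm to be known weeks ahead. Because it can be, each pre-operative decision to leave, to postpone or to reconsider may be made by someone who knows the allocation. No blinded or independent review of those decisions is described.

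Re-judgement is a realistic event. Section 7.1.1 accepts eligibility tests up to 360 days old at registration, and the only stated reconfirmation comes before the arm is assigned.

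The same departures before allocation would be screening attrition and could not bias the comparison. After allocation, a patient who is not operated on leaves the primary analysis. If departures differ by arm and the leavers differ in prognosis, the two FAS groups are no longer the randomised groups. The exits also disturb the minimisation balance and draw on the dropout allowance.

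**Working it through.** **1. Can the arm be known before each exit?**

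| Event before surgery | Effect on participation | In the FAS? |
|---|---|---|
| Consent withdrawn | Ends (7.6 item 2) | No, if not operated on |
| Laminoplasty judged not indicated | Ends (7.6 item 3) | No, if not operated on |
| No surgery by day 90 | Ends (7.6 item 1) | No if never operated on; unclear if operated on later, because 10.1.1 does not say whether late surgery counts |
| Eligibility lapses through worsening | Surgeon decides (7.1.3), although 7.6 items 3 and 6 may also apply | Depends on that decision |

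All four can happen after the arm is displayed.

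**2. The plan's own sample size (section 10.2).** Inputs: SD 40, margin 20, one-sided alpha 0.025, power 0.90. A true difference of 0 is my assumption, since none is stated.

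- Normal approximation: n per arm = 2 × 40² × (1.960 + 1.282)² / 20² = 84.1, so 85 per arm, 170 in all.
- Noncentral t: 85 per arm gives power 0.8999 and 86 gives 0.9032, so 86 per arm, 172 in all. This matches the plan.
- Dropout: 172 / 0.80 = 215, or 216 with equal arms. This also matches.
- Allowance: 216 − 172 = 44 patients (20.4%), not divided between pre-operative exits and later loss.

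**3. Numbers lost (rates assumed).** With 3% to 8% leaving before surgery, 216 × 0.03 = 6.5 and 216 × 0.08 = 17.3, so about 6 to 17 patients come out of the 44. If 5% leave before surgery and 20% of the rest are lost later, 216 × 0.95 × 0.80 = 164 remain and power is 0.89. With 10% and 20%, 156 remain and power is 0.87.

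**4. Bias (rates assumed).** Let a share f of an arm leave before surgery, and let those patients, had they been operated on, have recovered g points less than those who stay. The FAS mean of that arm then exceeds its all-randomised mean by f × g. With the same g in both arms, the between-arm difference shifts by (difference in f) × g.

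- Difference in f of 0.05, g = 20: 0.05 × 20 = 1.0 point.
- Difference in f of 0.05, g = 30: 0.05 × 30 = 1.5 points.

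**5. Effect on one-sided error.** With 86 per arm, SE = 40 × √(2/86) = 6.10. At a true difference of −20, the chance of declaring non-inferiority is Φ(−1.96 + bias/SE) when the bias favours the suture anchor.

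| Bias (points) | Bias/SE | One-sided error |
|---|---|---|
| 0 | 0 | 0.025 |
| 1.0 | 0.16 | 0.036 |
| 1.5 | 0.25 | 0.043 |

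Bias in the other direction would lower the error and cost power.

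**The case against.** **Ninety days is a maximum.** Section 6.2 admits only patients already scheduled for laminoplasty, section 7.1.2 has eligibility reconfirmed before registration, and allocation the day before surgery is already allowed. This stands: nothing shows that long gaps will be usual. But the protocol permits them and sets no earliest date.

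**Not every such patient drops out.** A reader might infer that they all do. The documents do not support that: section 7.1.3 lets some patients with lapsed eligibility stay in, and section 10.1.1 does not clearly exclude a patient operated on after day 90. Nor is it stated that patients are told the arm at registration; the display is to study staff, and the patient's knowledge is only implied by the open design.

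**Dependence on the arm is not demonstrated.** Whether laminoplasty is indicated concerns an operation that both arms receive, and section 13.2 expects no difference in difficulty, complications or safety. Against this, section 3.2 cites reports of superior fixation strength with plates, so a preference is plausible. Its strength and direction are unknown.

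**The effect is small.** A shift of 1 to 1.5 points is 5% to 7.5% of the margin. At 3% overall loss, a 5-point gap would mean about 5.5% against 0.5%, so nearly all losses would fall in one arm. The assumed 6 to 17 exits fit within the allowance of 44. The ANCOVA in section 10.5.2 also adjusts for age, sex and diagnosis, three of the four minimisation factors, leaving only facility out. All of this limits the size of the problem without removing it.

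**The FAS definition is the deeper cause.** This is partly right: exits matter mainly because the FAS requires surgery, and consent can be withdrawn after any allocation, however late. Yet an analysis set based on all randomised patients would still lack outcomes for those who leave, whereas later allocation prevents many such losses.

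**Conclusion.** The point holds as a weakness in the timing of allocation that should be corrected. The protocol allows the arm to be known for up to 90 days before surgery, and exits in that time, where no operation follows, remove patients from the primary comparison.

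A reader might go further and infer that the result will be biased towards non-inferiority. The documents do not support that: they contain no rate of pre-operative loss, no difference between arms and no prognosis for those who leave. The 1 to 1.5 points, and the error of 0.036 to 0.043, rest on the assumed 5-point gap, the assumed 20 to 30-point deficit and a direction favouring the suture anchor. The power loss is modest under the assumed rates, and the stated 172 and 216 are unaffected. The case for change is that the exposure is largely avoidable at low cost. The timing of allocation is fixed by the protocol, and a later analysis plan cannot undo decisions already made with the arm known.

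**What to change.** - **Sections 5.3 and 7.1.2:** separate registration from allocation in the EDC. Register after consent as now. Run the minimisation and display the arm only after the surgery date is set and eligibility has been reconfirmed, within a short stated window before surgery and at the latest the day before. The minimisation itself should run at that point; hiding a result computed at registration would not protect the balance. Patients who leave earlier then count as registered but not randomised.
- **After allocation:** keep every randomised patient in follow-up, subject to consent, and report pre-operative exits by arm with reasons. Section 7.6 lets a withdrawing patient have all data destroyed, so this account may be incomplete.
- **Reconcile sections 7.1.3, 7.6 and 10.1.1:** state whether a randomised patient operated on after day 90, or whose eligibility lapsed before surgery, remains in follow-up and in the FAS. This concerns data retention and analysis; the treatment-timing rule itself is left as it is.

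**Cost:** an EDC configuration change and a protocol amendment, with no change in sample size. Sites must have both implant sets available, or be able to order within the window, and the window should be chosen with that in mind. Both methods are insurance-covered (section 15.1), and allocation the day before surgery is already permitted, so this should be workable, although the documents do not describe site stocks.

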**7.1.3　Protocol Treatment**

- Protocol treatment (cervical laminoplasty) must be performed within 90 days of registration.
- If protocol treatment cannot be performed within 90 days for any reason, enter the reason for discontinuation in the case report form as “Protocol Treatment Discontinued”.
- If eligibility criteria are no longer met due to worsening of the primary disease or comorbidities between registration and the protocol treatment date (surgery date), the decision to continue study participation and perform surgery as protocol treatment is left to the discretion of the attending surgeon. The case report form must document that eligibility criteria were no longer met during the period from registration to the treatment date, along with details.
- Laminoplasty for DCM is performed using either the mini-plate or the suture-anchor.
- Surgery is performed under general anesthesia.
- A midline longitudinal skin incision is made from C2 to C7 in the prone position. Dissection is performed up to the medial facet joints.
- Perform a double-opening laminoplasty, expanding 2-4 laminae on the C3-6 vertebrae.
- Resect the tips of the spinous processes to expand the laminae. Use a high-speed drill to make a median longitudinal split in the midline of the laminae. Use the high-speed drill to create a groove at the medial aspect of the intervertebral joints, achieving a suitable hardness for lamina expansion. After creating a median longitudinal split and groove on all planned laminar expansions, gradually expand the lamina using a mucosal elevator. Medially transect the elevated ligamentum flavum, dissect adhesions to the dura mater, and confirm decompression by observing dura mater bulging. Control bleeding from the epidural venous plexus as needed.
- The attending surgeon shall perform the enlarged lamina fixation using either the plate method or the suture anchor method, according to the assignment results at registration.
- Dome-shaped laminectomy may be added to the cephalad and caudal laminae during lamina enlargement.
- Place a drain on the posterior aspect of the lamina prior to closure. Specifications and duration of drain placement are not stipulated.
- Regardless of any concomitant procedures, operative time, blood loss, and intraoperative/postoperative complications shall be included in the surgery. Details shall be recorded in the medical record (or surgical report) and case report.
- For methods other than the expanded lamina fixation technique, the surgical team shall perform the procedure using the settings and methods they deem optimal (see 7.1.4).
- Participation in the study requires that a Japanese Society of Spine Surgery and Related Research (JSSR) certified spine and spinal cord surgery instructor be employed at each participating institution.
- The attending surgeon shall perform surgery using the assigned enlarged lamina fixation method (plate method/suture anchor method) whenever possible. If a different enlarged lamina fixation method is used than the assigned group, the reason must be entered in the case report form. (See 7.1.4)

The procedures for the plate method and suture anchor method are outlined below.

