| **Protocol Treatment** | [figure not shown]  The principal investigator (or designated surgeon) will perform surgery (mini-plate or suture-anchor) according to the allocation results. Surgery will be performed by an orthopedic surgeon experienced in cervical laminoplasty. The surgical method and pre- and postoperative evaluation schedule are as follows.  **【Surgical Method】**  Under general anesthesia, a midline longitudinal skin incision is made from C2 to C7 in the prone position. Dissection is performed up to the medial facet joints. A double-door laminoplasty is performed on the laminae of C3-6, enlarging 2-4 laminae.  Dome-shaped laminectomy of C2 and C7 is added as needed.  ＜Control Group＞ Mini-Plate  Screws are placed in the expanded laminae at C3-6, and a plate is applied. Screw and plate sizes are determined according to the lamina shape in each case.  ＜Experimental Treatment Group＞ Suture-Anchor  An anchor is placed in the lateral mass at any level from C3-6. Sutures are applied to the ligamentum flavum and sutured to maintain the expanded position.  **[Pre- and Postoperative Evaluation Schedule]**  1) Pre-operative: X-ray, CT, MRI, clinical evaluation  2) Postoperative 1 week: CT  3) Postoperative 1 year: X-ray, CT, MRI, clinical evaluation, direct medical costs  4) Postoperative 2 years: X-ray, CT, MRI, clinical evaluation, direct medical costs |
| **Target Study Population** | 216cases |
| **Research Period** | Total Research Period: October 17, 2025 (jRCT Publication Date) to March 31, 2031 (5.5 years)  (Planned Registration Period: 3 years, Follow-up Period: 2 years after registration completion, Analysis Period: 0.5 years) |
| **Number of Research Facilities** | 3 facilities (Institute of Science Tokyo Hospital, Saiseikai Kawaguchi General Hospital, Saku Medical Center) |

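### The extent of surgery (2-4 laminae, optional dome laminectomy) is recorded only as performed, after the arm is known, yet it defines a subgroup and bears on how operative time and blood loss are read

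*Protocol*

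**What the plan says.** **Timing.** Section 5.2.1 declares the trial non-blinded. Under section 5.3 the subject's number and assigned fixation method "will be displayed in the EDC system and also recorded in a printable/downloadable PDF file". Section 7.1.2 sets the latest point: "Registration and randomization must be completed by the day before surgery". Section 7.1.3 sets the longest interval: "Protocol treatment (cervical laminoplasty) must be performed within 90 days of registration".

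**Extent.** Section 7.1.3 gives a range and no rule for choosing within it: "Perform a double-opening laminoplasty, expanding 2-4 laminae on the C3-6 vertebrae". On dome laminectomy the Overview says "Dome-shaped laminectomy of C2 and C7 is added as needed", and section 7.1.3 says "Dome-shaped laminectomy may be added to the cephalad and caudal laminae during lamina enlargement". Apart from the fixation itself, section 7.1.3 leaves methods to the surgical team's judgement. The only reference to a plan is in the description of the operation: "After creating a median longitudinal split and groove on all planned laminar expansions".

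**Recording.** In section 7.2.2 the laminoplasty levels and the presence of dome laminectomy are listed under Surgical Information, which the schedule in 7.2.1 places on the day of surgery. Patient Background Information includes the level of maximum stenosis but no planned levels. Planned extent is not among the minimization factors in 5.3.

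**Use.** Section 7.1.3 counts concomitant procedures in operative time and blood loss. Section 10.5.3 compares both by Student's t-test. Section 5.1 justifies these endpoints as direct measures of how simple the technique is. Section 10.5.4 lists the number of expanded laminae, in classes of 2, 3 and 4, as a subgroup factor.

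**The concern.** A subgroup factor should be a baseline characteristic, so that within each class the arms remain comparable by randomization. The number of laminae actually expanded does not have that guarantee. It is recorded at surgery by a team that knows the arm, and nothing recorded beforehand shows whether it moved.

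For operative time and blood loss the issue is interpretation. If one arm happened to receive more levels or more dome laminectomies, the t-test would combine the extra decompression with the time and bleeding due to the fixation. Section 5.1 wants to learn about the second. Adjusting for the performed extent would not separate them cleanly, because performed extent is itself a post-allocation variable. Planned extent recorded before allocation would be a proper baseline covariate. The protocol's data items do not include it, and an analysis plan written later could only approximate it.

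**Working it through.** **1. Order of events, from the text.**

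| Step | When | Section |
| --- | --- | --- |
| Baseline imaging and stenosis level | up to 360 days before registration | 7.1.1, 7.2.1, 7.2.2 |
| Arm displayed | registration | 5.3 |
| Surgery | 1 to 90 days after registration | 7.1.2, 7.1.3 |
| Levels and dome laminectomy recorded, as performed | day of surgery | 7.2.1, 7.2.2 |

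A plan is implied but has no stated date and no listed data item. So extent may be fixed before the arm is known, or may be settled or altered afterwards. The recorded data could not distinguish these cases.

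**2. The plan's own figure.** Section 10.2 uses SD 40%, margin 20%, one-sided alpha 0.025 and power 0.9. With the noncentral t, noncentrality = 20 / (40 × √(2/n)). At n = 86 per arm the power is 0.903, so 172 in total, as stated. 86 / 0.8 = 107.5, rounded up to 108 per arm, or 216. The sample size reproduces, and this point does not touch it.

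**3. What imbalance would matter for operative time or blood loss.** Only n comes from the protocol. Suppose the fixation makes no difference at fixed extent, and a difference in extent shifts the arm means by d standard deviations. The two-sided 5% t-test has standard error √(2/n) SD and noncentrality d × √(n/2).

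| n per arm | SE (SD units) | d for 7.5% rejection | d for 10% rejection |
| --- | --- | --- | --- |
| 108 | √(2/108) = 0.136 | 0.063 | 0.089 |
| 86 | √(2/86) = 0.152 | 0.071 | 0.100 |

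The row for 108 is the more relevant, since operative time and blood loss are known at surgery and do not wait for one-year follow-up.

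**4. Conversion to levels.** The protocol gives no effect of one extra lamina or dome laminectomy on these endpoints. Assume e SD per extra level. The difference in mean levels that yields d = 0.089 is 0.089 / e:

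- e = 0.2: 0.089 / 0.2 = 0.45, or one extra level in 45 more patients per 100 in one arm
- e = 0.3: 0.089 / 0.3 = 0.30, or 30 per 100
- e = 0.5: 0.089 / 0.5 = 0.18, or 18 per 100

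At the other end, a difference of 0.1 levels with e = 0.2 gives d = 0.02 and rejection of about 5.2%, which is negligible.

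**The case against.** The case on the other side is substantial, and much of it stands.

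- **The stronger reading is not in the text.** A reader might infer that the number of laminae is chosen after the arm is known. No section says so. Patients are already scheduled for laminoplasty at enrolment (6.2), and 7.1.3 speaks of planned expansions. The wording that dome laminectomy may be added during enlargement could merely describe the operative step. The protocol leaves the choice open; it does not place it after allocation.
- **No arm-linked mechanism is given.** Both arms require at least two implants, and 7.1.3 describes decompression as a step common to both. No stated reason exists for an arm to receive more levels.
- **The t-test is not wrong as such.** Randomization protects the comparison of assigned strategies. If assignment altered extent, the test would correctly report the total effect of assignment. The rejection rates above are false positives only for a fixation effect at fixed extent. Section 5.1 leans towards that reading, but the protocol does not define it as the target.
- **Some information survives.** Preoperative X-ray, CT and MRI, stenosis level and dural sac area allow partial adjustment for anatomical need. Surgical plans may also exist in medical records. What limits this is that "data obtained within 360 days prior to registration may be used", and that a stenosis level is not a surgical plan.
- **The subgroups are labelled exploratory** and carry no confirmatory claim.

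What remains is that a non-baseline variable defines a subgroup, and that a simple field which would have supplied the baseline version is not listed.

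**Conclusion.** The point holds as an optional improvement to data capture, not as a demonstrated flaw. The subgroup by number of expanded laminae is defined by a variable recorded after allocation in an open-label trial. The t-tests of operative time and blood loss measure the simplicity of the fixation only if extent is balanced between arms.

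The direction and size of any distortion cannot be derived from the protocol. The break-even of 0.089 SD at 108 per arm follows from the sample size alone. Its translation into 18 to 45 extra levels per 100 patients rests on an assumed 0.2 to 0.5 SD per level. An imbalance of that size would be large, and nothing in the document predicts one. A reader might also infer that these comparisons are biased, or that the non-inferiority result is at risk. The document supports neither: no imbalance is shown, and the primary JOA conclusion, the margin and the sample size are unaffected.

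**What to change.** 1. In 7.1.2 and 7.2.2, add EDC fields for planned laminoplasty levels and planned dome laminectomy, to be completed before the allocation is displayed.
2. In 7.1.3, leave surgical freedom as it is, but record any departure from the plan with its reason. Report planned against performed extent by arm.
3. In 10.5.4, define the laminae subgroup by the planned number.
4. In 10.5.3, analyse operative time and blood loss with planned levels and planned dome laminectomy as baseline covariates. These are likely to be prognostic, so precision may also improve.

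The cost is a few fields and short text edits. A plan entered early in the 90-day window may be provisional. Because registration is allowed until the day before surgery, sites can limit this by registering later; otherwise changes simply appear as recorded departures. The fields must be in place before enrolment, or early in it, since a plan written down after the arm is known no longer serves as a baseline variable.
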